## Abstract

**Background:**

Practice guidelines (PGs) are systematically developed statements intended to assist in patient, practitioner, and policy decisions. The AGREE II is the revised and updated standard tool for guideline development, reporting and evaluation. It is comprised of 23 items and a user's Manual. The AGREE II is ready for use.

**Objectives:**

To develop, execute, and evaluate the impact of two internet-based educational interventions designed to accelerate the capacity of stakeholders to use the AGREE II: a multimedia didactic tutorial with a virtual coach, and a higher intensity training program including both the didactic tutorial and an interactive practice exercise component.

**Methods:**

Participants (clinicians, developers, and policy makers) will be randomly assigned to one of three conditions. *Condition one, didactic tutorial *-- participants will go through the on-line AGREE II tutorial supported by a virtual coach and review of the AGREE II prior to appraising the test PG. *Condition two, tutorial + practice *-- following the multimedia didactic tutorial with a virtual coach, participants will review the on-line AGREE II independently and use it to appraise a practice PG. Upon entering their AGREE II score for the practice PG, participants will be given immediate feedback on how their score compares to expert norms. If their score falls outside a predefined range, the participant will receive a series of hints to guide the appraisal process. Participants will receive an overall summary of their performance appraising the PG compared to expert norms. *Condition three, control arm *-- participants will receive a PDF copy of the AGREE II for review and to appraise the test PG on-line. All participants will then rate one of ten test PGs with the AGREE II. The outcomes of interest are learners' performance, satisfaction, self-efficacy, mental effort, and time-on-task; comparisons will be made across each of the test groups.

**Discussion:**

Our research will test innovative educational interventions of various intensities and instructional design to promote the adoption of AGREE II and to identify those strategies that are most effective for training. The results will facilitate international capacity to apply the AGREE II accurately and with confidence and to enhance the overall guideline enterprise.

## Introduction

Evidence-based practice guidelines (PGs) are systematically developed statements aimed at assisting clinicians and patients to make decisions about appropriate health care for specific clinical circumstances [1] and to inform decisions made by health care policy makers and clinical managers [2,3]. In systematic reviews, guidelines have been shown to have a modest impact on behavior [4]. However, the potential benefits of their application are only as good as the guidelines themselves [5-7]. To enable differentiation between PGs of varying quality and to advance the PG enterprise, the AGREE (Appraisal of Guideline Research and Evaluation) collaboration was established to facilitate the development of a generic instrument to assess the process of PG development. Using rigorous methodologies of measurement construction [8], the AGREE collaboration produced the original AGREE Instrument released in 2003 [[9]; http://www.agreetrust.org].

As with any new development tool, it was recognized that on-going methodological refinement of the AGREE instrument was required. This led to the establishment of a second international group of researchers, the AGREE Next Steps Consortium. The consortium undertook a program of research with the objectives of strengthening the measurement properties of the instrument, refining some of the items, systematically exploring its utility across stakeholders, and improving the supporting documentation to help users implement the instrument with more confidence. The results of these efforts are the AGREE II [[10-12]; http://www.agreetrust.org]. The AGREE II consists of 23 items grouped into the six original domains: scope and purpose, stakeholder involvement, rigour of development, clarity of presentation, applicability, and editorial independence. Compared to the original AGREE instrument, approximately one-half of the items have been modified, domain structures have been altered, and an extensive restructuring of the supporting documentation, the user's manual, was undertaken. A new seven-point response scale has also been introduced, replacing the original four-point scale. The AGREE II was released at the Guidelines International Network Fall 2009 Colloquium and is ready for use.

Diffusion of the original instrument attests to its wide coverage and acceptance but also highlights the complexity of successfully facilitating the uptake of the revised version. In conducting an analysis of the ISI Web of Science (unpublished), we found 139 citations of the original AGREE paper between its publication in 2003 and December 2008, with numbers increasing every year. Lead authors represented 23 different countries and publications appeared in 95 different peer-reviewed journals -- both specialist and generalist publications. The citations represented a wide spectrum of diseases and disciplines, including cancer, cardiology, diabetes, dentistry, psychiatry, and occupational medicine.

We anticipate the demand for the AGREE II will be as high. We are promoting the AGREE II to a broad constituency and the dissemination plan is international in focus. The target audience includes a variety of stakeholder groups (clinicians, researchers, policy makers, PG developers, system leaders) and, within groups, a range of experience with PGs and the AGREE enterprise (*i.e.*, from novice to expert). Thus, the internet is a key medium for our knowledge translation and exchange (KTE) strategy. However, dissemination alone, even with a primed and interested audience, is not sufficient to maximize the application and use of the AGREE II.

Thus, we wish to explore educational interventions and leverage technical platforms to accelerate the process. E-learning (internet-based training) provides a potentially effective, standardized, and cost-efficient model for training in the use of AGREE II. A recent meta-analysis and systematic review of 201 studies by Cook *et al. *showed large effect sizes for internet-based instruction (clinical and methodological content areas) with health-profession learners [13]. Most of the studies considered knowledge outcomes and found evidence of a substantial benefit. Those studies reporting a skills outcome, however, also found a very large effect size for e-learning interventions. The findings held true in subgroup analyses comparing different learner types, contexts, topics and outcomes. Thus, e-learning appears to be a promising, effective, practical, and efficient KTE technique to consider in our context, and we will test two interventions aimed at facilitating the application of the AGREE II.

Key evidence-based principles exist that underpin the development of technical training and multimedia learning to which we will adhere. The Instructional Systems Development framework, including the ADDIE (analysis, design, development, implementation, and evaluation) model of instructional development will serve as our approach in the design and refinement stages of our intervention [14]. The work by Clark *et al. *will inform the structure and specific content types that will be incorporated [15-18]. Narration choices, contiguous labeling, and the use of graphics will follow the principles of multimedia learning [17,19]. Principles derived from cognitive load theory will also be taken into consideration in the design of the educational interventions [16,20].

In a meta-analysis and systematic review of instructional design variations in web-based learning, Cook *et al. *found that increased interactivity, practice exercises, repetition, and feedback were associated with improved learning outcomes [13]. However, while the evidence base underpinning the efficacy and design principles of internet-based training materials are well established, there remain questions regarding the optimal application of these principles for particular interventions. For example, both worked examples (demonstrations) and practice exercises with feedback have been shown to be effective training methods [17]. Yet some evidence suggests that novice learners may benefit more from worked examples, and expert learners more from practice [16,18]. Moreover, many recommended instructional design interventions such as interactivity, practice exercises, or repetition may take longer to develop, and also take up more of the learners' time, potentially leading to less efficient training. In developing an optimal on-line training intervention for the AGREE II, we also aim to study some of these key instructional design variables and time-on-task.

Our research objectives are: to design and refine an on-line AGREE II training program comprised of a multimedia didactic overview tutorial; to design and refine an on-line, interactive AGREE II training program, comprised of the overview tutorial plus an interactive practice exercise with feedback module; to compare the two interventions against a standard control (access to static PDF version of the user's manual) and to evaluate learners' performance (distance function to experts, pass/fail rate), satisfaction, self-efficacy, mental effort, and time-on-task with the AGREE II; and to compare how previous experience with PGs and the AGREE II influence these effects.

Two core research questions are considered: Compared to the passive learning of the materials, does an on-line training program, with or without a practice exercise, improve learners' performance and increase learners' satisfaction and self-efficacy/-confidence with the AGREE II and AGREE II user's manual? Are there differences across the outcome measures between the two educational intervention groups? Are these differences influenced by learners' experiences with PGs or the AGREE II?

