### Study design

A single factorial design with three levels of educational intervention is proposed. The levels are:

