### Sample Size

The primary analysis involves one-way analysis of variance (ANOVA) comparisons of the AGREE II performance score profiles of the three study group participants with the performance score profiles of AGREE II experts. This will be measured by the sum of squared deviations (SS) distance function. To avoid untenable assumptions regarding the relative size of the intermediate group mean, we simplify calculations by focusing on the power for testing differences in mean SS between the passive learning condition and either of the intervention groups, which represents a strong *a priori *comparison of the least and most effective interventions. Previous research has found the effect size of e-learning in comparison to no intervention to be large ranging from 1.13 to 1.50 [16-18]. Our intent is to estimate a more conservative effect size. Thus, with 20 participants per group, a one-sided test will have at least 80% power to detect an advantage of as little as ± 0.79 standard deviations for either of the intervention groups compared to the passive learning group. To account for potential missing data, we will include up to 25 participants per group for a total of 75 participants in the study.

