### Analyses

#### Performance -- distance function

Our primary outcome for performance will be a measure of distance in AGREE II item and domain rating profiles of the participants versus rating profiles of experts. The distance function will be calculated as the sum of the squared deviations (SS) between expert scores and participant's scores, summed over AGREE II items (SSi) and, alternatively, domains (SSd). Such a measure offers a precise and integrated summary of similarity over the whole profile of responses, and it provides a standard quadratic weighting of errors, consistent with other widely used measures of agreement, such as weighted kappa. Since the SS is typically skewed, we will use its square root in analysis. A series of one-way ANOVA tests will then be conducted to examine differences in distance function as a function of educational intervention.

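### The sample size is justified for a one-sided comparison with passive learning, but the primary analysis is an undirected three-group ANOVA that has less power and answers neither core question

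*Protocol article*

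**What the plan says.** The Introduction sets out directed comparisons. The first is "Compared to the passive learning of the materials, does an on-line training program, with or without a practice exercise, improve learners' performance". The second is "Are there differences across the outcome measures between the two educational intervention groups".

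The design has one factor with three arms: "A single factorial design with three levels of educational intervention is proposed".

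The Sample Size section opens with the primary analysis: "The primary analysis involves one-way analysis of variance (ANOVA) comparisons of the AGREE II performance score profiles of the three study group participants". It then bases the calculation on a different test, "focusing on the power for testing differences in mean SS between the passive learning condition and either of the intervention groups", which it describes as a strong a priori "comparison of the least and most effective interventions". The power claim follows: "with 20 participants per group, a one-sided test will have at least 80% power" for a difference of 0.79 SD. Up to 25 per group (75 in total) are to be enrolled to allow for missing data.

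Under Performance -- distance function, the analysis of the primary outcome is: "A series of one-way ANOVA tests will then be conducted to examine differences in distance function as a function of educational intervention". The Learner's scales section repeats the one-way ANOVA for the learner outcomes, and pass/fail is compared with a chi-square statistic. The Analyses section names no contrast or pairwise comparison.

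**The concern.** A three-group F test asks only whether all three means are equal. It has no direction, so it cannot be the one-sided test for which the sample size was justified. A significant result also does not say which arm differs from which.

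Two things are at stake. First, the advertised power does not belong to the analysis that is called primary. Second, the primary p-value would support neither conclusion the trial is meant to reach. The comparison with passive learning at least appears in the power argument. Practice versus tutorial, which decides whether the more intensive programme is worth its extra time, appears only as a question.

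The power argument is itself ambiguous: the least against the most effective intervention is one pair, while passive learning against either intervention is two.

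**Working it through.** **Inputs.** From Sample Size: 20 per group, difference 0.79 SD, one-sided, at least 80% power. From Study design: three groups. Alpha is not stated; 0.05 is assumed throughout. Means are in SD units with equal variances.

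**1. The plan's own figure.** The noncentrality for one pair is 0.79 × √(20/2) = 2.498.
- Normal approximation, one-sided 0.05: Φ(2.498 − 1.645) = Φ(0.853) = 80.3%.
- Noncentral t: 79.1% with 38 df (two groups) and 79.5% with 57 df (variance pooled over three groups).
- Two-sided 0.05: Φ(2.498 − 1.960) = 70.5%; noncentral t with 57 df gives 69.0%.

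The stated 80% therefore reproduces for a single one-sided comparison at 0.05, and not for a two-sided one.

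**2. Power of the stated primary analysis.** For the omnibus F with 2 and 57 df, the critical value is 3.159 and λ = n Σ(μᵢ − μ̄)².
- Middle arm halfway (0, 0.395, 0.79): λ = 20 × (2 × 0.395²) = 6.241, power 57.8%.
- Middle arm equal to either extreme (0, 0, 0.79 or 0, 0.79, 0.79): λ = 20 × (2/3 × 0.79²) = 8.321, power 71.1%.

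If all 25 per group are evaluable, these become 68.7% and 81.4%. The 80% claim, however, is made at 20 per group.

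**3. Error rates if pairs are tested.** From 1,000,000 simulated null trials, 20 per group, pooled variance, 0.05 per test, two-sided:

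| Pairs tested | Regardless of F | Only after a significant F |
|---|---|---|
| Two comparisons with passive | 9.0% | 4.2% |
| All three pairs | 12.1% | 5.0% |

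When passive learning truly differs and the two training arms are equal, the F-gated false-positive rate for practice versus tutorial is at most about 5%.

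**4. Power of a pairwise contrast under different rules** (0.79 SD, 20 per group, 57 df)
- One-sided, unadjusted: about 79%.
- Two-sided, unadjusted: about 69%.
- Two one-sided comparisons with passive, Bonferroni: about 69%.
- Two-sided, gated on F, middle arm halfway: about 56%.
- Tukey over three pairs: about 54%.

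**5. Practice versus tutorial.** The 95% CI half-width is 2.002 × √(2/20) = 0.63 SD. If the tutorial arm lies halfway, the true difference is 0.395 SD and a direct two-sided test has about 23% power.

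**The case against.** The best defence is that a journal article need not list follow-up tests, and that a fuller protocol or analysis plan, not shown here, may do so. The Sample Size section speaks of ANOVA comparisons and calls passive learning versus an intervention an a priori comparison, so the first question is not wholly without a test. This stands against any complaint of mere omission. It does not remove the conflict inside the article, which states both the primary analysis and the powered test, and they differ.

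A reader might infer that the trial faces a false-positive rate of 9% to 12%. The documents do not support that. Those rates apply only to pairs tested at 0.05 whatever the F result, and the article plans no such tests. With exactly three groups, pairs tested only after a significant F hold the familywise rate at about 5%, so the ANOVA can itself serve as the gate. The article states no gate either, so the rates are a reason to choose a rule and not an error already made.

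A reader might also infer that every outcome rests on ANOVA. Pass/fail does not.

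Nor is the F test always weaker than a planned contrast. With the middle arm at either extreme its 71% slightly exceeds the 69% of a two-sided unadjusted contrast. It remains below the stated 80% in both configurations at 20 per group.

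**Conclusion.** The point holds as a mismatch between the research questions, the powered test and the stated primary analysis. At 20 per group and 0.79 SD, the ANOVA has about 58% to 71% power, depending on where the middle arm lies, against the 80% claimed. A significant F would not by itself establish that training beats passive learning or that practice adds to the tutorial. The latter comparison has neither a named test nor a power statement in the article.

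The figures assume alpha 0.05, normal outcomes with equal variances on the analysed scale, and 20 evaluable participants per group. The mismatch itself does not depend on them. It should be corrected before the data are seen, because it determines what the trial can conclude.

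**What to change.** Under Performance -- distance function, name three contrasts from the same ANOVA model as the primary inference: tutorial versus passive, tutorial with practice versus passive, and tutorial with practice versus tutorial. Report each difference with a 95% CI.

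State alpha, sidedness and one error-control rule. Testing pairs only after a significant F is enough with three groups. Tukey covers all three pairs. Dunnett covers the two comparisons with passive learning, so practice versus tutorial would then need its own stated rule. A strict fixed sequence with practice versus tutorial last is possible but serves that question poorly: with two-sided tests and the middle arm halfway, it is reached in about 21% of trials and all three steps succeed in 1.7%.

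In Sample Size, say which pair or pairs the power refers to, and restate it for the rule chosen, using the figures in the working.

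The change is to wording and needs no new data. Its cost is candour about power. Under any rule stricter than a single one-sided unadjusted test, the figure falls clearly below 80% at 20 per group. Practice versus tutorial will remain imprecise and should be presented mainly through its interval.

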### Study design

A single factorial design with three levels of educational intervention is proposed. The levels are:

### Didactic tutorial

Participants assigned to this training program condition will receive access to a password-protected website. They will receive a brief (five-minute) multimedia didactic tutorial with an overview of the AGREE II conducted by a 'virtual coach' or avatar. The tutorial is under program control with forced linear progression in sequence with the screens advancing automatically, although the participant may pause the tutorial at any time. Following the tutorial, the participant is granted access to the AGREE II user's manual and is instructed to review the manual before proceeding to the test PG.

### Tutorial with practice exercise

Participants assigned to this training condition will receive access to a password-protected website. They will be provided with the same didactic tutorial as the previous condition before being granted access to the user's manual as above. They will then be presented with a practice PG to appraise using the AGREE II training tool and will be asked to answer each AGREE II item in turn. Upon entering their AGREE II score, participants will be given immediate feedback on how their score compares to the mean of four experts. If their score falls outside a predefined range, participants will receive formative feedback to guide the appraisal process. At the conclusion of their review, participants will receive an overall summary of their performance in appraising the practice PG compared to expert norms before proceeding to the test PG.

### Passive learning

Participants assigned to the passive learning will receive static PDF copies of the AGREE II for review before proceeding to the test PG. Passive learning participants will serve as our control group.

### Sample Size

The primary analysis involves one-way analysis of variance (ANOVA) comparisons of the AGREE II performance score profiles of the three study group participants with the performance score profiles of AGREE II experts. This will be measured by the sum of squared deviations (SS) distance function. To avoid untenable assumptions regarding the relative size of the intermediate group mean, we simplify calculations by focusing on the power for testing differences in mean SS between the passive learning condition and either of the intervention groups, which represents a strong *a priori *comparison of the least and most effective interventions. Previous research has found the effect size of e-learning in comparison to no intervention to be large ranging from 1.13 to 1.50 [16-18]. Our intent is to estimate a more conservative effect size. Thus, with 20 participants per group, a one-sided test will have at least 80% power to detect an advantage of as little as ± 0.79 standard deviations for either of the intervention groups compared to the passive learning group. To account for potential missing data, we will include up to 25 participants per group for a total of 75 participants in the study.

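### The stated 80% power is for a one-sided two-group comparison; the planned three-group ANOVA has about 58–71% power at the same 0.79 SD

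*Protocol article*

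**What the plan says.** Under Study design, the protocol article sets out one factor at three levels: "A single factorial design with three levels of educational intervention is proposed". Sample Size names the primary test: "The primary analysis involves one-way analysis of variance (ANOVA) comparisons of the AGREE II performance score profiles of the three study group participants". The Analyses section, under the distance function, repeats this: "A series of one-way ANOVA tests will then be conducted to examine differences in distance function as a function of educational intervention".

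Sample Size then departs from that test for the power calculation. To avoid assuming where the intermediate group mean lies, the authors write that "we simplify calculations by focusing on the power for testing differences in mean SS between the passive learning condition and either of the intervention groups". They describe this as a strong a priori comparison. The result, for 20 participants per group, is that "a one-sided test will have at least 80% power to detect an advantage of as little as ± 0.79 standard deviations". Up to 25 per group (75 in total) are to be recruited to allow for missing data. No significance level is given. The Analyses section plans one-way ANOVAs, chi-squared tests for pass/fail and exploratory covariate analyses, but no one-sided contrast of an intervention with control.

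**The concern.** The test that was powered and the test that is planned are different. A one-sided two-group comparison spends its whole error rate in one direction on one difference. The F test of a three-group ANOVA has two numerator degrees of freedom and no direction, so at the same alpha it needs a larger effect for the same power. The article leaves out the intermediate mean because any assumption about it would be untenable. That is safe only if the two-group figure is a lower bound for the ANOVA whatever the third mean is.

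If it is not, the article gives no power for its own primary analysis, and a reader will naturally carry the 80% over to it. A non-significant ANOVA could then be read as fair evidence against a benefit of 0.79 SD, when the chance of missing such a benefit is larger than the 20% the figure suggests.

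**Working it through.** **Inputs.** From Sample Size: 20 per group for the power statement, up to 25 per group recruited, difference 0.79 SD (SD = 1), one-sided, 80% power. From Study design: three groups. Alpha is not stated; 0.05 is assumed because it is the value that reproduces the stated figure, and 0.10 is shown as a variant.

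**1. The plan's own figure.**
- Normal approximation: detectable difference = (1.645 + 0.842) × √(2/20) = 0.786 SD, which rounds to 0.79. Power at 0.79 is 80.3%.
- Exact noncentral t: noncentrality = 0.79 × √(20/2) = 2.498. Power is 79.1% with 38 df (two groups) and 79.5% with 57 df (error variance pooled over three groups).
- The same comparison two-sided: 70.5% (normal), 68.3% (t, 38 df), 69.0% (t, 57 df).

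So the stated 80% reproduces to within about one point, as a one-sided two-group test at 0.05. A two-sided test at 0.05 does not give it.

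**2. The planned ANOVA at the same effect.** Power comes from the noncentral F with 2 and 3n − 3 df and noncentrality λ = n × Σ(μᵢ − μ̄)².
- Third mean halfway, means (0, 0.395, 0.79), n = 20: λ = 20 × (0.395² + 0 + 0.395²) = 20 × 0.31205 = 6.24. Against the critical value F(2, 57) = 3.16, power is **57.8%**.
- Both interventions at full effect, means (0, 0.79, 0.79), n = 20: μ̄ = 0.5267; λ = 20 × (0.5267² + 2 × 0.2633²) = 20 × 0.41607 = 8.32. Power is **71.1%**. It is the same if only one intervention works, means (0, 0, 0.79).

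The halfway position gives the smallest λ and the extremes the largest. With a largest difference of 0.79 SD and n = 20, no position of the third mean within that range reaches 80%. The two-group figure is therefore not a lower bound for the ANOVA.

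**3. Sensitivity of the ANOVA result.**

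| Setting | Third mean halfway | Third mean at an extreme |
|---|---|---|
| n = 20, alpha 0.05, 0.79 SD | 57.8% | 71.1% |
| n = 20, alpha 0.10, 0.79 SD | 70.1% | 81.3% |
| n = 25, alpha 0.05, 0.79 SD | 68.7% | 81.4% |
| n = 20, alpha 0.05, 1.13 SD | 88.6% | 95.8% |
| Difference with 80% power, n = 20, alpha 0.05 | 1.01 SD | 0.87 SD |
| Evaluable n per group for 80% at 0.79 SD, alpha 0.05 | 32 | 25 |

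**4. If the contrasts with control were primary.** There are two comparisons with a shared control, n = 20 and 57 df. Dunnett critical values at familywise 0.05 are about 1.95 (one-sided) and 2.27 (two-sided). With noncentrality 2.498, power per comparison is about 71% one-sided and 59% two-sided. Without adjustment, two one-sided 5% tests give a familywise error of about 8.7%.

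**The case against.** The strongest reply is that nothing is hidden. The article says it is simplifying, gives its reason and ties the 80% to a one-sided comparison. It never says the F test has 80% power. A reader might infer that the authors miscalculated, or that they claim 80% for the ANOVA; the text supports neither. The calculation is right for the test it describes.

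A second reply is that the research question is directional (does training improve performance over passive learning), so a planned contrast within the ANOVA is a natural reading, and a journal article may leave the list of contrasts, alpha and multiplicity to a fuller document. This stands in part: the absence of alpha or of a multiplicity rule is not itself the fault. But the article does state its primary test, in two places, and both times it is the three-group ANOVA.

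A third reply is that 0.79 SD is a deliberately cautious target below the 1.13–1.50 cited in Sample Size, and that up to 25 per group will be recruited. Both facts reduce the practical risk. They do not remove the mismatch, because the power statement itself rests on 20 per group and 0.79 SD, and the extra participants are there to cover missing data.

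The ± sign beside a one-sided test, and the use of either intervention arm in a sentence about the least and most effective ones, might be read as further contradictions. They are loose wording: at equal group sizes and a common SD, the pairwise power is the same whichever arm is compared with control.

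**Conclusion.** The point holds as a mismatch between the test that was powered and the test that is planned. The stated power is correct for a one-sided two-group comparison at an assumed alpha of 0.05. It does not carry over to the primary ANOVA, which at 0.79 SD with 20 per group and the same assumed alpha has 58–71% power, a 29–42% chance of missing an effect of that size.

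The size of the gap depends on the unstated alpha, the position of the third mean and the number evaluable. At alpha 0.10 with 20 per group, or at 0.05 with all 25 evaluable, the ANOVA reaches 80% only when the third mean lies near an extreme. A reader might go further and conclude that the trial is underpowered in general. The documents do not support that: at 1.13 SD, the lower end of the cited effects, the ANOVA has about 89–96% power with 20 per group.

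**What to change.** Make Sample Size and Analyses describe the same test, in one of two ways.

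1. **Keep the ANOVA as primary and restate its power.** For example: *With 20 evaluable participants per group and alpha 0.05, the one-way ANOVA has 80% power for a largest difference between groups of about 0.87 to 1.01 SD, depending on the intermediate group; at 0.79 SD its power is 58–71%.* If another alpha is intended, state it and recompute.
2. **Make the intervention-versus-control contrasts primary.** Name them in the distance-function section of Analyses, state alpha, sidedness and multiplicity control, and quote their power. Under Dunnett at 0.79 SD with 20 per group this is about 71% per comparison one-sided, or about 59% two-sided.

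In either case drop the ± sign if the test stays one-sided. The first option changes only the sample-size paragraph; the second also changes the Analyses text. Neither needs more participants. The cost is a less favourable stated figure. Holding 80% for the ANOVA at 0.79 SD would instead take 25 to 32 evaluable per group, which is a separate decision.
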